### Description of other study procedures and follow-up

Only patients presenting acutely to study PHCs, that is, those without scheduled appointments, will be screened for eligibility. The app will use skip logic and contain prompts for the healthcare worker to check patient eligibility, allowing recruitment and data collection only when the requisite conditions are met.

Patients can be enrolled multiple times during the study period, as the primary objective is to determine the proportion of presentations which result in antibiotic prescription. However, they cannot be re-enrolled if they are within the follow-up period (defined below), as any attendances within this period will be logged as unscheduled re-presentations; this is a secondary outcome measure. If all the following identifiers of a patient are exact matches with those of another patient currently under follow-up, the healthcare worker will confirm that they are not the same person: date of birth (or age if date of birth is not known), gender and village of residence. Only once this confirmation is provided can the patient be enrolled.

All patients will have a medical history taken and will be examined as per normal practice. In intervention arm PHCs, this process will be more structured as it will be guided by EDAM. Practice will remain unchanged in control arm PHCs.

Patients will be followed up by telephone at 7 days post presentation (allow +2 days); patients who have not recovered by day 7 will be followed up at day 14 (+2 days). The following data will be collected at follow-up:

Recovery (self-reported).If not recovered, whether symptoms were better, worse or the same.Whether they re-presented to another healthcare provider (re-presentations to the same PHC should be captured by the EDAM app).If they re-presented, whether they were hospitalised and (if known) whether antibiotics were prescribed.

Should a patient be uncontactable by telephone after three attempts, SEACTN village health workers will be used to locate the patient and conduct the follow-up interviews at day 7 and day 14, as necessary, if the participant survived, and document death, if the participant did not survive. If this is unsuccessful, the patient will be deemed lost to follow-up.

One important caveat is that patients who re-present during the follow-up period will be considered as unscheduled attendances secondary to the initial diagnosis, given that unscheduled attendance is a secondary outcome measure. This will also allow determination of whether antibiotics are initially withheld and then given at a subsequent visit. The major limitation of this approach, however, is that some patients may be categorised as unscheduled presentations when their subsequent visit is actually for a new problem or illness.

The trial schedule of enrolment, interventions and assessments, completed using the Standard Protocol Items: Recommendations for Interventional Trials (SPIRIT) guideline template,^27^ is shown in table 2. The completed SPIRIT checklist can be found in online supplemental information S2.

**Table 2 T2:** Schedule of enrolment, interventions and assessments

Timepoint (DAY)	Study period			
	Enrolment	Clinical encounter	Follow-up	
	0	0	7	14
Enrolment:				
Eligibility screen	X			
Interventions:				
EDAM app		X		
Standard of care		X		
Assessments:				
Antibiotic prescription		X		
Hospital referral		X		
Recovery by day 7			X	
Recovery by day 14 (if not recovered by day 7)				X
Death or hospitalisation* by day 7			X	
Death or hospitalisation* by day 14 (if not recovered by day 7)				X
Re-presentation by day 7			X	
Re-presentation by day 14 (if not recovered by day 7)				X
Antibiotic consumption† by day 7			X	
Antibiotic consumption† by day 14 (if not recovered by day 7)				X

* If not referred to hospital at the time of clinical encounter.

† If not prescribed antibiotic at the time of clinical encounter.

EDAM, Electronic clinical Decision support for Acute fever Management

The trial commenced in May 2024. The end date is dependent on the rate of patient enrolment but will be no later than May 2025.

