## Methods and analysis

### Design

This is a pragmatic, cluster-randomised controlled trial with two study arms consisting of 15 PHCs in the intervention (EDAM-guided clinical management, further details of which are provided below) arm and 15 PHCs in the control (standard care) arm. A PHC will be considered as a cluster, and the assignment of PHCs to arms will be randomly performed by computer. The pragmatism of the study was confirmed using the PRagmatic Explanatory Continuum Indicator Summary−2 tool,^20^ with the majority of the study design domains rated ‘very pragmatic’ (online supplemental information S1).

The rationale for this study design is that any study assessing the potential performance of eCDSAs like EDAM must necessarily be pragmatic and conducted in environments as similar to real-world conditions as possible. Otherwise, in a research-oriented context, healthcare worker prescribing and other management practices may be consciously or unconsciously affected. Furthermore, for policy-makers to consider wide-scale eCDSA implementation, what is most needed is a pragmatic implementation study of its impact in routine care. As such, this study will evaluate the introduction of EDAM into routine care with no research staff routinely present. To minimise disruption and alteration of routine care, a waiver of written patient informed consent was requested from the relevant ethics committees, in accordance with the 2016 WHO/CIOMS International Guidance for Health-related Research Involving Humans. In brief, the 2016 CIOMS Guideline 10 states that in the following circumstances a waiver of informed consent could be applied^21^:

if the research would not be feasible or practicable to carry out without the waiver or modification;if the research has important social value; andif the research poses no more than minimal risks to participants.

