### Description of intervention

The intervention is the EDAM app deployed on tablet devices, which uses data on clinical features including vital signs and pulse oximetry with malaria and CRP rapid tests to guide primary healthcare workers in their clinical decision-making when confronted with patients with AFI, plus training required for effective use of the app. This training will include familiarisation with the app interface, as well as measurement and interpretation of vital signs, CRP rapid tests and pulse oximetry.

For the purposes of this study, the EDAM app was constructed using the CommCare platform (Dimagi, Cambridge, USA). This platform was chosen for familiarity reasons among primary healthcare workers with an established link to SEACTN, as it was also used to construct the electronic data collection tool used in SEACTN.

As part of screening, patients presenting to a PHC in the intervention arm will have their demographic details logged on the EDAM app. Assessment of study eligibility will be performed by a healthcare worker. If the patient is eligible for enrolment, vital signs, including measurement of peripheral oxygen saturation using pulse oximetry, will be performed. One of three possibilities may then ensue:

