Healthcare workers in intervention arm PHCs will be provided with face-to-face training on the use of EDAM. They will also be taught how to use pulse oximeters and CRP rapid tests, which are not available in control arm PHCs, as well as trained on measuring blood pressure, respiratory rate and pulse rate, and assessing level of consciousness. Training will be conducted by the study team in the relevant local language prior to patient recruitment, with refresher training conducted on the advice of site coordinators or study monitors. Contact details of the study coordinator and/or field supervisor will be provided to PHCs; these personnel will be available for advice should any queries regarding the study arise.

To maintain clinical practice and workflows at control arm PHCs as close to the current standard of care as possible, the only extra activity for the trial required of healthcare workers in the control arm is screening and data collection. They will receive a simplified version of the EDAM app which will allow them to log patient demographic details as well as conduct patient screening and enrolment, but does not contain the clinical decision support algorithms present in the version used in the intervention arm. Control arm healthcare workers will receive training in the use of the simplified EDAM app, but not in the clinical procedures and use of point-of-care aids that healthcare workers in the intervention arm are taught.

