### Description of statistical analyses

The primary endpoint is the proportion of patient consultations for AFI which result in antibiotic prescription. The primary comparison between the treatment arms will be a logistic regression with the treatment assignment as a fixed effect, and the PHC as a random effect. P values (two-sided) below 0.05 are considered significant. A two-sided 95% CI for the OR of being prescribed antibiotics will be calculated.

The primary endpoint (proportion of patients given an antibiotic prescription) will also be investigated by subgroup to assess whether any change in antibiotic prescribing is homogeneous across subgroups. Specifically, intervention effects and appropriate tests for heterogeneity will be calculated in the following predefined subgroups:

Age: younger children aged ≥1 to <5 years, older children aged 5 to <15 years and adults aged ≥15 years.Sex at birth: male or female.Patients with a documented fever or hypothermia at presentation versus patients without.

The secondary endpoints will be analysed in a similar manner to the primary endpoint. A detailed Statistical Analysis Plan will be developed prior to the completion of recruitment for the study.

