### Data management

Data will be captured electronically through the EDAM app and submitted to a central server. A data dictionary will be constructed in which all variables are clearly explained. A logbook of patients screened and recruited will also be maintained.

Patients will be assigned a unique composite ID number each time they are enrolled. They will be identified only by their unique ID number on study documents, in data entry and in any electronic databases in order to protect their privacy. The only patient-identifying data entered in the logbooks will be the names of patients, their villages of residence and their telephone numbers, for the purposes of carrying out follow-up. No other identifiers will be collected, and these details will not be entered into any databases held or accessed by the study team. All documents will be stored securely and only accessible by study staff and authorised personnel. Any scientific publications or reports will not identify any individual participant/s by name or initials.

Electronic data will not be modifiable by the healthcare worker after submission, although authorised users, for example, site research staff will be able to do so for data cleaning purposes. Access to the data will be password protected. Direct access will be granted to authorised representatives from the University of Oxford, the study site partners and the respective national ethics committees for monitoring and/or audit of the study to ensure compliance with regulations.

The database and all electronic data will be routinely backed up. In accordance with MORU Standard Operating Procedures, deidentified electronic data will be stored indefinitely on the central server, while paper records will be preserved for 5 years.

Healthcare workers will be trained prior to study commencement on collection of data using the version of the EDAM app relevant to their PHC. Training materials, for example, videos will be uploaded to the tablet devices in case they need to refer to these.

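### PHC staff who know their arm screen and enrol; no check is stated that eligible patients enter equally in both arms, and the primary model adjusts for no patient characteristics

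*Protocol article*

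**What the plan says.** All references are to the protocol article.

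- **Who recruits.** Description of intervention: "Assessment of study eligibility will be performed by a healthcare worker". Under Design, EDAM is evaluated in routine care "with no research staff routinely present".
- **Whether staff know the arm.** The end of Description of intervention says of the intervention arm: "Training will be conducted by the study team in the relevant local language prior to patient recruitment". It says of control staff: "They will receive a simplified version of the EDAM app", without the algorithm. PHCs are the unit of randomisation (Design; Sample size calculations). Both groups therefore know their arm when they screen.
- **What the app enforces.** Description of other study procedures and follow-up says it will "contain prompts for the healthcare worker to check patient eligibility, allowing recruitment and data collection only when the requisite conditions are met".
- **What is intended.** Description of intervention has presenting patients in intervention PHCs logged at screening and eligible ones enrolled, with or without danger signs. Description of other study procedures has unscheduled presenters screened. Control staff are required to screen and collect data.
- **When recruitment stops.** Status and timeline: at the target for each cluster, which is 152 (Sample size calculations).
- **What records exist.** Data management: "A logbook of patients screened and recruited will also be maintained". Safety considerations mentions remote and on-site monitoring under a monitoring plan.
- **The primary model.** Description of statistical analyses: "a logistic regression with the treatment assignment as a fixed effect, and the PHC as a random effect". Age group, sex, and documented fever or hypothermia appear only as subgroups.

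**The concern.** In a cluster trial, randomisation balances the clusters. It balances the patients analysed only if each arm captures the same kind of patient. Here the people entering patients know their arm, and the task differs between arms. Intervention staff take vital signs and oximetry, follow an algorithm, sometimes run a CRP test, and record reasons for disagreeing. Control staff only screen and log. The Introduction itself lists heavy workload, threats to autonomy and poor workflow fit as known barriers to tools of this kind.

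If the mix of enrolled patients differs by arm, recorded prescribing will differ even if EDAM changes nothing, or a true effect will be diluted. The PHC random effect does not help. Each PHC belongs to one arm, so a shift common to all PHCs of an arm is attributed to treatment. Intention-to-treat analysis covers only patients who were enrolled.

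**Working it through.** **1. The plan's own figure.** Inputs from Sample size calculations: 25% vs 17.5%, two-sided 5%, power 80%, ICC 0.025, 15 clusters per arm, 10% drop-out.

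- Individually randomised n (pooled variance) = 466 per arm.
- Cluster size m = n(1 − ICC)/(k − n·ICC) = 466 × 0.975/(15 − 466 × 0.025) = 454.35/3.35 = 135.6, rounded up to 136.
- After drop-out: 136/0.9 = 151.1, rounded up to 152. Total 30 × 152 = 4560.

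The stated size reproduces exactly. The yardstick for any bias is the planned 7.5-point difference.

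**2. Is there room for selection?** Setting asks for PHCs likely to see at least 150 AFI patients in 4–6 months, which is 25 to 37.5 a month. Over the expected 6–9 months that gives 25 × 6 = 150 to 37.5 × 9 ≈ 338 patients. A target of 152 is then anywhere from 152/338 = 45% to effectively all of them. These are bounds at the minimum qualifying volume, not predictions. A PHC that enrols everyone stops early, and a busier PHC has more room.

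**3. Effect of missed patients, with no true effect.** Let s be the fraction of eligible intervention patients not entered and q their prescribing rate. Neither is in the documents. The enrolled rate is (0.25 − s·q)/(1 − s). With s = 10%:

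| q (assumed) | Enrolled rate | Spurious fall | Share of 7.5 points |
|---|---|---|---|
| 40% | (0.25 − 0.04)/0.9 = 23.3% | 1.7 points | 22% |
| 50% | (0.25 − 0.05)/0.9 = 22.2% | 2.8 points | 37% |
| 60% | (0.25 − 0.06)/0.9 = 21.1% | 3.9 points | 52% |

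**4. The opposite direction.** Apply the same selection to the control arm and let EDAM truly achieve 17.5%. The observed difference shrinks from 7.5 points to 23.3 − 17.5 = 5.8, 22.2 − 17.5 = 4.7, or 21.1 − 17.5 = 3.6 points.

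**5. On the odds-ratio scale.** Suppose intervention PHCs enrol patients who would get an antibiotic with relative probability r compared with other eligible patients, the same r in each PHC. The odds in those PHCs are multiplied by r, so the unadjusted OR is r. For q = 50%, r = (1 − 0.05/0.25)/(1 − 0.05/0.75) = 0.80/0.933 = 0.86. For q = 40% and 60%, r = 0.91 and 0.80.

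The chance of a significant result favouring EDAM with no true effect was taken by normal approximation. The effective n per arm is 15 × 136.8/4.395 ≈ 467, where 136.8 = 152 × 0.9 and 4.395 = 1 + 135.8 × 0.025.

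| r (assumed) | Intervention rate | Share of planned effect | Chance of significance |
|---|---|---|---|
| 0.9 | 23.1% | 26% | about 10% |
| 0.8 | 21.1% | 53% | about 30% |
| 0.7 | 18.9% | 81% | about 61% |
| 0.636 | 17.5% | 100% | about 80% |

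The scenarios in step 3 therefore correspond to roughly a 10–30% false-positive chance, against 2.5% in that direction by design.

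**The case against.** The strongest reply is that the text reads as an all-presenters rule: presenters are logged, acute cases are screened and eligible patients are enrolled. A reader might infer from the set-up that workers choose whom to open on the app, or that the logbook holds only patients they chose to screen. The documents say neither, nor do they say that the enrolling worker is always the prescriber. This stands, and the point is put as a risk for that reason.

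Other parts of the reply also carry weight:

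- The waiver of written consent removes one familiar source of recruitment bias.
- Leaving research staff out is a reasoned choice, made to avoid altering prescribing.
- For patients with danger signs the algorithm ends at once, so workload gives little reason to bypass it for them.
- PHCs near the minimum volume have little room to miss patients.
- Age and sex do not identify patients likely to be given antibiotics, so covariates are the smaller part of the remedy.

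It may also be said that the analysis plan and monitoring plan, which are not shown, could cover this. They may add sensitivity analyses or completeness checks. But this article already fixes the primary model without covariates, and it does not connect the logbook or the monitoring to completeness by arm. The stated limitations do not mention selective enrolment.

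**Conclusion.** The concern holds as a risk of unknown size and direction. Staff aware of their arm control entry, the app guards only against ineligible entries, and no comparison of enrolled with eligible patients by arm is stated. The primary model corrects none of the measured imbalance that could follow. Under the assumption that 10% of eligible intervention patients are missed with 40–60% prescribing among them, the enrolled rate falls by 1.7–3.9 points with no true effect. Mirror-image selection would hide a similar amount of a real one.

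Two stronger readings are not supported. One is that differential enrolment is taking place or will favour EDAM; nothing in the article gives a rate or a direction. The other is that the missing covariates cause the problem and adding them would solve it. They would remove only the imbalance they measure, and most of a severity-driven imbalance could remain.

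**What to change.** 1. **Primary model.** Add age group and sex as fixed effects. Age and sex are basic details available in both arms, and both are already predefined subgroups. Keep the unadjusted model as a sensitivity analysis.
2. **Documented fever or hypothermia.** Use it only in a further sensitivity model. It is measured after randomisation by staff who know the arm, and only the intervention arm is trained in clinical measurements, so its recording could itself differ by arm.
3. **Enrolment completeness.** At the monitoring visits already planned, count AFI consultations from the PHC patient logbooks (already a source for site selection) over each PHC's own recruitment window. Report enrolled over AFI consultations, and baseline characteristics, by arm.
4. **Prespecified sensitivity analysis if the fractions differ.** For an enrolled fraction f and enrolled rate p, the rate among all eligible is f·p + (1 − f)·q. Vary q separately by arm and report where the conclusion changes. A range for q is needed because the article says routine prescribing data in these PHCs are scarce.

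The article places the analysis plan before the end of recruitment, so these choices can be fixed there, with the change of primary model documented as an amendment. The cost is a little monitor time and an OR that is conditional on age group and sex as well as PHC; an adjusted risk difference can be reported beside it. The logbook counts depend on how consistently fever is recorded, which the article does not describe.

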### Participant characteristics

Healthcare workers will be advised that use of EDAM should be restricted to patients within a recommended target population. This target population comprises patients meeting all the following inclusion and exclusion criteria.

The inclusion criteria are as follows:

Age ≥1 year.Unscheduled presentation for acute care.Documented fever (≥37.5 °C axillary) or hypothermia (<35.5 °C) or history of fever in the last 24 hours.

The exclusion criteria are as follows:

Onset of illness >14 days.Presenting due to accident or trauma.Presenting ≤3 days after routine immunisations.Presenting within the follow-up period.

Should a patient not meet all criteria, enrolment will not be permitted by the internal logic of the EDAM app. The app will advise healthcare workers in intervention arm PHCs to continue standard practice for non-eligible patients.

Investigators may discontinue a participant from the study at any time if considered necessary for any reason, including but not limited to:

Ineligibility (either arising during the study or having been overlooked during screening).Significant protocol deviation.Significant non-compliance with study requirements.

The reason for withdrawal will be recorded. Data from withdrawn participants will be included in the intention-to-treat (primary) analysis but not in any per-protocol analyses.

Participants have the right to withdraw from follow-up at any time.

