### Outcome measures

The primary outcome measure is the proportion of patients with AFI who are prescribed antibiotics in routine primary healthcare at initial presentation in the intervention and control arms.

Several secondary outcome measures will also be assessed:

The proportion of patients with full recovery at 7 and 14 days in intervention and control PHCs.The proportion of patients referred to hospital at presentation in intervention and control PHCs.The proportion of patients in intervention PHCs whose management followed the EDAM recommendations.The proportion of patients with unplanned re-presentations to any healthcare facility at 7 and 14 days (if not fully recovered by 7 days) in intervention and control PHCs.The proportion of patients prescribed antibiotics by a healthcare provider or who independently purchased antibiotics during the follow-up period, as determined by self-report, in intervention and control PHCs.The proportion of patients with severe clinical outcomes (death or hospitalisation) at 7 and 14 days (if not fully recovered by 7 days) in intervention and control PHCs, not including those referred to hospital at presentation.The proportion of patients prescribed an antibiotic in intervention PHCs by CRP level (<10 mg/L, between 10 and 80 mg/L, >80 mg/L).The usability and acceptability of EDAM for healthcare workers (a separate ethical approval application will be made for this work).The cost-effectiveness of EDAM compared with routine care.

Interpretation of the outcomes will consider the contextual factors inherent to the Cambodian primary care landscape, as described by Chew *et al*.^31^ In addition, the usability and acceptability of EDAM will be measured using structured interviews conducted with the healthcare workers in the intervention arm; this study does not form part of this protocol and will have its own ethical approval, as mentioned previously.

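### Returns to the enrolling PHC count towards the re-presentation outcome, but only app entries by its own staff record them, because the follow-up contact does not ask the patient

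*Protocol article*

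**What the plan says.** The Protocol article, Outcome measures, defines a secondary outcome as "The proportion of patients with unplanned re-presentations to any healthcare facility at 7 and 14 days (if not fully recovered by 7 days"). The enrolling PHC is a healthcare facility, so a return there counts.

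The section Description of other study procedures and follow-up lists what is collected by telephone at day 7 and, for those not recovered, at day 14. The relevant item is "Whether they re-presented to another healthcare provider (re-presentations to the same PHC should be captured by the EDAM app"). The next item, on hospitalisation and antibiotics, applies to those who re-presented.

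For the enrolling PHC, the same section says that "any attendances within this period will be logged as unscheduled re-presentations; this is a secondary outcome measure". It also describes a check before enrolment: "If all the following identifiers of a patient are exact matches with those of another patient currently under follow-up, the healthcare worker will confirm". What the worker confirms is that the two records belong to different people. The identifiers are "date of birth (or age if date of birth is not known), gender and village of residence". Separately, the exclusion criteria under Participant characteristics include "Presenting within the follow-up period".

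On village, Data management lists names, villages and telephone numbers as the identifying details written in logbooks, and says that "these details will not be entered into any databases held or accessed by the study team".

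**The concern.** The outcome has two components, returns to other providers and returns to the enrolling PHC, and each has a single source. The patient reports the first. The second depends on a busy health worker opening the app for someone who cannot be enrolled, recognising the earlier visit and logging it. The Design section says that research staff will not normally be on site. No step is described in which the patient's account would reveal a visit that was not logged.

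A patient sent home without antibiotics may well go back to the same PHC. The article relies on such visits to learn whether antibiotics were withheld at first and given later. If they are under-recorded, a safety-related secondary outcome looks better than it is. If they are under-recorded unequally, the comparison between arms is distorted. A return that nobody recognises could also be enrolled as a new presentation and so enter the primary analysis, which counts consultations.

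**Working it through.** **Text check**

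1. Outcome: any facility (Outcome measures).
2. Contact: another provider only (follow-up list).
3. Same PHC: left to the app (same list). Call and app together are meant to cover any facility, so the gap lies in ascertainment and not in the definition.
4. Recognition of a return: either the worker applies the exclusion criterion, or the app finds an exact match and asks the worker to confirm. Both routes need the worker to use the app. If both fail, for example because a different age is given and the worker does not recall the patient, the visit can be enrolled under a new ID.
5. Arms: both use an app for screening and enrolment. The control version has no decision support (Description of intervention), so the incentive to open it for a returning patient may differ.
6. Antibiotics: the follow-up list attaches the question to re-presentation, directly after the item limited to other providers. The outcome is defined by self-report and covers prescription by any provider or independent purchase.

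**The plan's own figure**

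No figure is given for this outcome. The primary sample size reproduces and is not affected:

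- 25% against 17.5%, two-sided 0.05, power 0.80, pooled variance: n = 465.8 per arm before clustering.
- With 15 clusters per arm and ICC 0.025: m = 465.8 × 0.975 / (15 − 465.8 × 0.025) = 135.4, rounded up to 136.
- With 10% drop-out: 136 / 0.9 = 151.1, rounded up to 152; 30 × 152 = 4560.

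**Illustration (all inputs assumed)**

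Let π be the true re-presentation rate, s the share of returns that go to the enrolling PHC, and c the fraction of those that are logged. Assume the call captures all other returns. Then

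recorded rate = π × [(1 − s) + s × c].

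Equal capture, π = 10%, s = 0.5, c = 0.5: 10% × (0.5 + 0.25) = 7.5% in each arm. There is no spurious difference, but the rate is understated by a quarter.

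Unequal capture (90% in one arm, 60% in the other), no true difference, s = 0.5:

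| True rate | Recorded at 90% | Recorded at 60% | Odds ratio |
|---|---|---|---|
| 5% | 4.75% | 4.0% | 1.20 |
| 10% | 9.5% | 8.0% | 1.21 |
| 20% | 19% | 16% | 1.23 |

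For true rates of 5% to 20% and s from 0.25 to 0.75, the spurious odds ratio runs from about 1.09 to 1.39, or 0.72 to 0.92 if the capture rates are swapped. With a milder gap, 90% against 70%, the spurious difference is 0.10 × 0.20 = 2 points if 10% of all patients return to the same PHC, and 0.05 × 0.20 = 1 point if 5% do.

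**The case against.** The strongest reply is that call plus app do cover any facility, that both arms are trained to screen with an app, and that a screening logbook and on-site and remote monitoring are planned. Call scripts and rules for merging sources often sit in the full protocol, which is not shown. Much of this stands, and it keeps the point small. It does not remove it, because the article states the choice outright: the patient is asked about other providers and the app is relied on for the rest.

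Four stronger readings are tempting, and the documents do not support them.

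- **That a return is captured only if the identifiers match exactly.** The match is written as a block on wrong re-enrolment. A worker who recognises the patient can apply the exclusion criterion without it.
- **That capture is known to differ by arm.** The stated difference between the apps is decision support, and nothing shows that logging of returns differs. The odds ratios above follow entirely from assuming unequal capture.
- **That the later-antibiotic outcome is biased in the same way.** Its definition rests on self-report and includes any provider, and Table 2 lists antibiotic consumption as its own follow-up item. What remains is a loosely worded question in the follow-up list. Nor do the documents show that the death or hospitalisation outcome is affected.
- **That the village statements flatly contradict each other.** The restriction concerns databases held or accessed by the study team. The app works offline, so matching on the device could satisfy both statements. The article does not say whether it does.

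**Conclusion.** The point holds as a minor weakness in how one secondary outcome is ascertained. Returns to the enrolling PHC are part of the outcome, rest solely on logging by PHC staff and have no described cross-check with the patient. The sure consequence is that any return left unlogged lowers the recorded rate. A difference between arms is possible, but its direction and size cannot be derived from the documents. Every figure in the illustration depends on assumed return rates, same-PHC shares and capture fractions.

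Enrolment of an unrecognised return as a new presentation is also possible. It needs both the worker's check and the match to fail, and its effect on the primary analysis cannot be sized from the article. The primary outcome definition and the sample size stand as they are.

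**What to change.** 1. At the existing day-7 and day-14 contacts, ask whether the patient returned to any provider, naming the enrolling PHC explicitly.
2. Ask about antibiotics from any source, independently of the re-presentation item, so that the question matches the self-report outcome.
3. Count a re-presentation if either the contact or the app shows it, with the same rule in both arms.
4. Reconcile Description of other study procedures and follow-up with Data management on whether village is held in the app, and if so whether only on the device.

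The cost is a slightly longer call, a written rule for merging two sources, and an amendment that both ethics committees must approve. The trial began in May 2024. If the change comes mid-trial, ascertainment changes part-way through, so it should start on the same date in both arms and be reported. If follow-up has already ended, comparing app entries with PHC logbooks in both arms is the remaining check.
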